| **Non-Inclusion**  **Criteria** | 1. Symptoms, physical signs of disease that could interfere with the interpretation of the trial results or compromising the health of the subjects 2. Immunosuppressive therapy (steroids, immune modulators or immune suppressors) within 3 months prior recruitment. (for corticosteroids, this will mean prednisone, or equivalent,  0.5 mg/kg/day. Inhaled and topical steroids are allowed.) 3. Cannot be followed for any social, psychological or geographical reasons. 4. Use of any investigational drug or vaccine other than the study vaccine within 30 days preceding the first dose of study vaccine, or planned use up to 30 days after the third dose. 5. Suspected or known hypersensitivity to any of the vaccine components or to previous vaccine. 6. Laboratory abnormalities on screened blood samples out of range, more specifically refer to table 2. 7. Planned administration of a vaccine not foreseen by the study protocol within 30 days before the first dose of vaccine. An exception, is the receipt of an EPI or licensed vaccine (measles, oral polio, Hib, meningococcal and combined diphtheria/pertussis/tetanus vaccines) which may be given 14 days or more before or after vaccination 8. Evidence of chronic or active hepatitis B infection 9. Presence of chronic illness that, in the judgement of the investigator, would interfere with the study outcomes or pose a threat to the participant’s health. 10. Administration of immunoglobulin and/or any blood products within the three months preceding the first dose of study vaccine or planned administration during the study period 11. History of surgical splenectomy. 12. Moderate or severe malnutrition at screening defined as weight for age Z-score less than ‑2 |
| **Investigational Product** | MSP 3 [181-276] LSP |
| ***Form*** | Adjuvanted with Alhydrogel in lyophilised form |
| ***Dose*** | 30µg or 15µg |
| ***Route*** | Subcutaneous, alternate deltoid region |
| **Control Product** | Hepatitis B |
| **Vaccination**  **Schedule** | Primary immunisation : day 0, 28; and 56 |
| **Follow-up duration** | One year after the first vaccination |
| **Blood sampling Schedule** | **D-28: (**screening)  **D0, D28 and D56**: (immediately before each vaccination)  **D84:** (28 days after third vaccination)  **D168:** (4 months after last vaccination)  **D 365:** (1 year after first vaccination) |

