| **Primary**  **Evaluation Criteria** | The primary endpoints are measures of the safety and reactogenicity of the vaccine as determined by:   1. Occurrence of solicited symptoms during a 7 day follow-up period after each vaccination (day of vaccination and 6 consecutives days) 2. • Occurrence of unsolicited symptoms during a 28 day follow-up period after each vaccination 3. • Occurrence of serious adverse events throughout the study period |
| **Secondary Evaluation Criteria** | 1. **Humoral response to vaccine antigens:**   Post vaccination levels of IgG, IgA and IgM, expressed in arbitrary units (ng/ml), relative to the pre-vaccination level (D0): D28/D0, D56/D0, D84/D0, D168/D0, and D365/D0.   1. **Cellular immune response to vaccine antigens:**   The number of cells producing IFNγ by Elispot expressed in number of spots /106 cells |
| **Exploratory Evaluation Criteria** | **To evaluate IgG ability to recognise the native protein on Merozoite by using WB**   - **Parasite inhibition by ADCI (SGI %) on D0, D84, D168 and D365. (only if isotype study shows the production of MSP3 specific cytophilic Abs in > 30% of volunteers)** |
| **Statistical Methods** | The analysis shall be descriptive  The final analysis is planned 1 month post Dose 3 to evaluate whether the safety GO/No GO criteria are met to proceed to a phase 2b in. An annex safety analysis will be performed at the end of the study, 9 months post Dose 3. |

| Study phases | Screening | Vaccination Phase (Double blind) | | | | | | | | | | Follow up (Single blind) | | |
| --- | --- | --- | --- | --- | --- | --- | --- | --- | --- | --- | --- | --- | --- | --- |
| Clinic Visit | **V1** | **V2** |  | **V3** | **V4** |  | **V5** | **V6** |  | **V7** | **V8** | **V9** |  | **V10** |
| **Home visits1** |  |  | **HV1-5** |  |  | **HV6-10** |  |  | **HV11-15** |  |  |  | **HV16-21** |  |
| **Trial Timelines (Days,)** | **D-28** | **D0** | **D1-D5** | **D6** | **D28** | D29-D35 | **D36** | **D56** | **D57-D62** | **D63** | **D84** | **D168** | **D196-D337** | **D365** |
| **Time Windows (Days)** |  |  4 D |  |  |  4 D |  |  |  4 D |  |  |  4 D |  7 D |  7 D |  14 D |
| **Study procedures** |  |  |  |  |  |  |  |  |  |  |  |  |  |  |
| Screening consent |  |  |  |  |  |  |  |  |  |  |  |  |  |  |
| Study Consent |  |  |  |  |  |  |  |  |  |  |  |  |  |  |
| Check of inclusion /non Inclusion Criteria |  |  |  |  |  |  |  |  |  |  |  |  |  |  |

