### Vaccination and serological schedule

Scheduled clinic visits are planned at day -28, 0, 6, 28, 36, 56, 63, 84, 168 and 365. Three vaccine doses will be administered by subcutaneous injection (day 0, 28 and 56). As shown in the flow chart (see page 9), participants will be monitored for the hour following vaccination, then a field worker will visit them at home on each of the 5 days following the injection. The patient will come back to the clinic at the 6th day following each immunization to be assess by a study clinician. Six serological blood sampling points have been planned on days 0, 28, 56, 84, 168 and 365.

Biological evaluations will also be done on days -28, 0, 6, 28, 36, 56, 63, 84 and 365. Apart from these standard examinations, other tests may be performed if deemed necessary.

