### Data Safety Monitoring Board (DSMB)

The DSMB for this study is a four member group of skilled professionals constituted according to AMANET procedures that respect international standards. These experts will monitor the progress of the study with particular interest in the safety of trial participants. Their composition, mandate and terms of reference are provided in the annexed DSMB charter.

Briefly, in this study, the DSMB will be responsible for:

- On going safety review and follow up in a unblinded manner
- Receive and review SAE’s when they occur
- Make recommendations to AMANET on the safety balance between the two comparison groups; and
- Make recommendations regarding continuing, amending or termination of the study for safety reasons.

The DSMB will receive progress reports one week after each injection within the first four months. SAE’s will be notified to the chair of the DSMB within 24 hours of the investigator learning of them.

The DSMB must be informed by AMANET as sponsor of the following safety data on an ‘as received’ basis:

- All SAEs;
- All withdrawals of study subjects by the Principal Investigator or the parent(s)/guardian(s) of a subject due to adverse events.

The DSMB will receive from the sponsor, AMANET:

- New information that may affect adversely the safety of the subjects or the conduct of the study;
- All subsequent protocol amendments, ICF changes or revisions of other documents originally submitted for review;
- All subsequent protocol modifications (for information).

The DSMB is empowered to suspend the enrollment to the trial and/or vaccination on the trial pending review of potential safety issues;

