# Primary evaluation criteria

## Definition of the Criterion

The reactogenicity and the safety shall be assessed on the following criteria:

1. Immediate reactogenicity (within 60 minutes, with emphasis on allergic reactions),
2. Local and systemic reactogenicity during the 7 days following each vaccination.
3. Any unsolicited adverse events (AE) occurring outside scheduled visit times, up to one month after the third vaccine dose and requiring a physician visit
4. Any serious adverse events (SAE) whenever they occur during the trial period (from first visit to last visit). The relationship with the vaccine must be determined by the investigator, using the following definitions: **not related, possibly related, probably related, definitely related.**
5. Biological safety, assessed four weeks after each injection, in relation to the baseline data profile on the following:

RBC, haemoglobin, haematocrit, platelets, WBC, Liver enzymes (SGOT, GPT, total bilirubin) and creatinine.

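### Safety-laboratory days differ between section 5.2.4, the synopsis blood-sampling list and primary criterion item 5, which names only the four-week values

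*Protocol*

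**What the plan says.** The places in the protocol that bear on the laboratory days do not agree.

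- **Section 5.2.4, Vaccination and serological schedule.** With doses on D0, D28 and D56: "Biological evaluations will also be done on days -28, 0, 6, 28, 36, 56, 63, 84 and 365". The same section lists the serological days separately: D0, D28, D56, D84, D168 and D365.
- **Synopsis, Blood sampling Schedule.** D-28 for screening; D0, D28 and D56 "immediately before each vaccination"; D84 ("28 days after third vaccination"); D168; D365. D6, D36 and D63 are absent.
- **Section 3, design diagram.** Blood samples at screening, the three vaccination days, D84, D168 and D365.
- **Section 14.1, item 5.** "Biological safety, assessed four weeks after each injection, in relation to the baseline data profile". The synopsis list of primary endpoints has no laboratory item.
- **Section 14.1, item 3.** "Any unsolicited adverse events (AE) occurring outside scheduled visit times, up to one month after the third vaccine dose and requiring a physician visit". The synopsis is wider: "Occurrence of unsolicited symptoms during a 28 day follow-up period after each vaccination".
- **Section 5.2.7.** "The DSMB will receive progress reports one week after each injection within the first four months".
- **Section 5.2.10.** The DSMB reports tabulate laboratory results by sampling point and toxicity grade, as far as 28 days after the second dose.
- **Section 13.2.** A laboratory abnormality becomes an AE or SAE when the investigator considers it clinically significant.

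**The concern.** Item 5 is the only part of the primary evaluation that takes laboratory values as such, and it names one time point per dose, at four weeks. Section 5.2.4 pays for a second look about a week after each dose, which is where a short-lived haematological, liver or renal change would be seen. As worded, the criterion does not use that second look. The synopsis list leaves it unclear whether the samples are to be taken at all.

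Two things are at stake. The first is what the primary laboratory safety result captures. The second is what the DSMB has in hand when it reviews a dose. Section 3 starts group 2 (30 µg) two weeks after group 1 (15 µg), and section 5.2.10 calls for a cumulative safety report before progression. Whether that report can contain any scheduled laboratory value taken after vaccination depends on which list is followed.

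**Working it through.** The protocol gives no figure for laboratory abnormalities, so there is none to reproduce. The detection probabilities in section 16.2 concern systemic reactions and SAEs and are not affected. The check compares the day lists.

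**Step 1. Interval since the preceding dose** (sample day minus dose day, with doses on D0, D28 and D56).

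| Day | Days since last dose | Safety labs, section 5.2.4 | Synopsis blood list | Item 5 | DSMB tabulation, section 5.2.10 |
|---|---|---|---|---|---|
| D6 | 6 − 0 = 6 | yes | no | no | yes, if drawn |
| D28 | 28 − 0 = 28 | yes | yes | yes | yes |
| D36 | 36 − 28 = 8 | yes | no | no | yes, if drawn |
| D56 | 56 − 28 = 28 | yes | yes | yes | yes |
| D63 | 63 − 56 = 7 | yes | no | no | no |
| D84 | 84 − 56 = 28 | yes | yes | yes | no |
| D168 | 168 − 56 = 112 | no | yes | no | no |
| D365 | 365 − 56 = 309 | yes | yes | no | no |

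D28 and D56 samples are taken before the dose given that day, so they belong to the preceding dose.

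**Step 2. Differences between the lists.** D6, D36 and D63 are in section 5.2.4 but not in the synopsis list. D168 is in the synopsis list but is not a safety-laboratory day in section 5.2.4. Section 5.2.4 also says the child returns on the sixth day after each dose, yet its own days fall 6, 8 and 7 days after.

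**Step 3. Share of points outside the criterion.** Up to D84, section 5.2.4 has six post-dose laboratory points: D6, D28, D36, D56, D63 and D84. Item 5 covers D28, D56 and D84. That leaves 3 of 6, or half, outside it.

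**Step 4. Where an early value can still go.**
- Clinically significant: it is an AE under section 13.2. The synopsis 28-day endpoint can take it in. Section 14.1, item 3 would not if it was found at a scheduled visit.
- Out of range but not judged clinically significant: no route into the primary criterion. D6 and D36 values appear in the DSMB tables.
- D63: after the cut-off of the specified DSMB tabulation and outside item 5. Only the AE/SAE route and the follow-up of Grade 3 and 4 values remain.

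**Step 5. Review before group 2 starts.** Group 2 is due on study day 14. Under the synopsis list, group 1's first post-dose sample is D28, and 28 > 14, so none is available. Under section 5.2.4 it is D6, and 6 < 14, so one is. More generally, under the synopsis list none of the one-week DSMB reports would hold a laboratory value taken after the dose under review.

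**The case against.** The strongest reply is that little is lost in practice. Section 13.1.1 counts an abnormal laboratory finding as a possible AE, section 13.2 records the clinically significant ones, and the synopsis primary endpoint takes unsolicited events for 28 days after each dose. Section 13.4.2.4 requires every Grade 3 or 4 laboratory abnormality to be followed until normal or explained. Section 5.2.10 already gives the DSMB all values through four weeks after dose 2. This stands. A reader might infer that a first-week abnormality would leave no trace in the safety results; the documents do not support that.

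A reader might also infer that the Go/No-Go decision rests on item 5 alone. That is unsupported too. The synopsis and section 5.2.3 say the analysis one month after dose 3 looks at safety data, and the protocol states no laboratory threshold.

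The conflict with the synopsis can also be questioned. Its flow chart has clinic visits at D6, D36 and D63 and rows for blood count and chemistry, but the marks in those rows are not readable here and may show the early draws. The blood-sampling list could be the six serological days plus screening. The section 3 diagram omits the D6, D36 and D63 visits altogether, so its silence on samples is weak evidence. In reply, the list is headed as the blood-sampling schedule and includes screening, so it is not purely serological. The narrow wording of item 5 does not depend on it.

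Finally, tabulation detail is properly left to an analysis plan. Which scheduled values a primary criterion counts is a protocol matter, and item 5 has already fixed it.

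**Conclusion.** The point holds in a limited form. Section 5.2.4, the synopsis blood-sampling list and section 14.1, item 5 give different laboratory days, and item 5 leaves out half (3 of 6) of the post-dose points up to D84 that section 5.2.4 schedules. What the primary criterion misses is early values that are out of range without being judged clinically significant. D63 values have the weakest cover, because they also fall outside the specified DSMB tabulation.

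The consequence for dose escalation is conditional. It holds if the synopsis list governs and the provisional two-week interval between groups is not lengthened to reach the D28 samples. The comparison with the synopsis rests on its blood-sampling list, not on the flow chart. Whether early abnormalities are common, and how many resolve by week four, cannot be judged from the protocol, and the point does not need it.

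**What to change.** Reconcile the synopsis blood-sampling list and flow chart, the section 3 diagram, section 5.2.4 and section 14.1, item 5 to one list of safety-laboratory days.

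- **If the early draws are kept:** reword item 5 to count all scheduled post-dose laboratory values, tabulated descriptively by time point and arm. Use toxicity grade where Table 1 in section 7.3 gives one (haemoglobin, white cells, platelets, ALT, creatinine) and out-of-range counts for the rest of item 5 (red cells, haematocrit, SGOT, bilirubin). Extend the laboratory tabulation in section 5.2.10 to post-dose-3 values.
- **If they are not kept:** delete D6, D36 and D63 from the laboratory days in section 5.2.4, and state that the review before group 2 starts is made without post-dose laboratory values unless the interval reaches the D28 samples.

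The cost is wording and slightly more descriptive tabulation. Keeping the early draws adds no samples to section 5.2.4. Measured against the synopsis list it means up to 3 × 45 = 135 more draws, if all 45 children have all three.

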## Parameters to be measured

The rate, duration and severity of signs and symptoms during the 7 days after each vaccination will be measured.

## Solicited symptoms

### Local reactions

The following local reactions will be solicited immediately after the injection (60 minutes) and over the 7 days following the vaccination (D1 and D7 follow-up) at the site of injection (left arm for 1st and 3rd injection; right arm for the 2nd injection) :

**Any local**

- 1. Pain at injection site
  2. Swelling at injection site
  3. Induration at injection site
  4. Erythema at injection site
  5. Pruritus at injection

### Systemic reactions

The following systemic reactions will be systematically solicited immediately after the injection (60 minutes) and during the 6 days following the vaccination (D1 to D6 follow-up).

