**PROTOCOL SYNOPSIS**

| **Sponsor legal name** | African Malaria Network Trust |
| --- | --- |
| **Finished product** | MSP 3 LSP malaria vaccine |
| **Active ingredient** | MSP 3 [181-276) LSP |
| **Trial Title:** | A double blind, randomized, controlled, dose escalation phase Ib field trial in 12 to 24 month old children in Burkina Faso to evaluate the safety and immunogenicity of the *Plasmodium falciparum* Merozoite Surface Protein-3 Long synthetic peptide (MSP 3) adjuvanted in aluminium hydroxide versus hepatitis B |
| **Trial Identifier:** | **MSP 3_BF_0302** |
| **Clinical phase** | Phase 1b |
| **Principal**  **Investigator** | [name] [name], BA, MD, PhD |
| **Investigators** | [name] MD  [name], PhD  [name]  [name], Pharm D, MSc  [name] Pham D, MSc  [name] Pharm D |
| **Biological**  **Evaluators**  **Biological supervisor** | [name], PhD  [name] MSc. |
| **Trial Centre(s)** | **Centre National de Recherche et de Formation sur le Paludisme**  [name]  BURKINA FASO  [contact] [contact] |
| **Planned Trial**  **Period** | March 2007 to February 2008 |
| **Primary Objective** | **To assess the safety and reactogenicity** of 3 doses of 15 µg and 30 µg MSP3 adjuvanted in aluminium hydroxide given at D0, D28 and D56 in healthy children aged 1-2 years old in Burkina Faso on the following :   1. Solicited adverse events    - immediate reactogenicity (within 1 hour, with emphasis on allergic reactions),    - local and systemic reactogenicity during 7 days following the vaccine injection (day of vaccination and 6 consecutives following days) 2. Unsolicited adverse events occurring within 28 days following each vaccination 3. Serious adverse events (SAE) whenever it occurs during the trial period (from first visit to last visit). |
|  |  |

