## Safety Data Collection and Reporting

### Expected Adverse Vaccine Reactions

As with any adjuvanted vaccine when administered subcutaneously, local reactions are expected. Systemic reactions are less often observed. Standardized data collection of adverse reactions will be organized as per AMANET ADR form.

The previous experience of MSP3 in study volunteers identified the following local reactions which should be monitored: pain, erythema, induration, pruritus, and swelling. There is a lack of information concerning expected systemic reactions; therefore, special attention will be given to general signs, i.e. fever, headache, malaise, fatigue, drowsiness, as well as signs of allergic reactions, i.e. urticaria, oedema, contra-lateral reactions, diffuse erythema.

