### Assessment of intensity

Intensity of the following AEs will be assessed as described:

Intensity scales for solicited symptoms in infants/toddlers and children less than 6 years of age

| **Adverse Event** | **Intensity grade** | **Parameter** |
| --- | --- | --- |
| Pain at injection site | 0 | Absent |
|  | 1 | Minor reaction to touch |
|  | 2 | Cries/protests on touch |
|  | 3 | Cries when limb is moved/spontaneously painful |
| Swelling at injection site | | Record greatest surface diameter in mm |
| Induration at injection site |  | Record greatest surface diameter in mm |
| Erythema at injection site |  | Record greatest surface diameter in mm |
| Pruritus at injection site | 0 | Absent |
|  | 1 | Easily tolerated by the subject, causing minimal discomfort and not interfering with everyday activities. |
|  | 2 | Sufficiently discomforting to interfere with normal everyday activities. |
|  | 3 | Prevents normal, everyday activities. |
| Fever* |  | Record temperature in °C |
| Irritability/Fussiness | 0 | Behavior as usual |
|  | 1 | Crying more than usual/ no effect on normal activity |
|  | 2 | Crying more than usual/ interferes with normal activity |
|  | 3 | Crying that cannot be comforted/ prevents normal activity |
| Drowsiness | 0 | Behavior as usual |
|  | 1 | Drowsiness easily tolerated |
|  | 2 | Drowsiness that interferes with normal activity |
|  | 3 | Drowsiness that prevents normal activity |
| Loss of appetite | 0 | Appetite as usual |
|  | 1 | Eating less than usual/ no effect on normal activity |
|  | 2 | Eating less than usual/ interferes with normal activity |
|  | 3 | Not eating at all |
| *Fever is defined as axillary temperature  37.5C | | |

The maximum intensity of local injection site swelling, induration and erythema will be scored as follows:

| 0 | None |
| --- | --- |
| 1 | < 5 mm |
| 2 | 5 to 20 mm |
| 3 | > 20 mm |

The maximum intensity of fever will be scored as follows:

| 0 | < 37.5°C |
| --- | --- |
| 1 | 37.5 – 38.0°C |
| 2 | > 38 – 39.0°C |
| 3 | > 39.0°C |
|  |  |

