**Any systemic**

1. Fever (defined as axillary temperature  37.5°C)
2. Drowsiness
3. Loss of appetite
4. Irritability/fussiness

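### The primary criterion stresses allergic reactions, yet the four allergic signs the protocol names are neither solicited nor graded, except as swelling or erythema confined to the injection site

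*Protocol*

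**What the plan says.** **The criterion.** Section 14.1 lists as its first item "Immediate reactogenicity (within 60 minutes, with emphasis on allergic reactions"). The primary objective in section 2 carries the same item. The synopsis also has it ("immediate reactogenicity (within 1 hour, with emphasis on allergic reactions")) and places it under solicited adverse events.

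**The signs to watch.** Section 13.4.1 explains that little is known about expected systemic reactions. It asks for particular attention to several general signs, "as well as signs of allergic reactions, i.e. urticaria, oedema, contra-lateral reactions, diffuse erythema".

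**What is solicited.** Section 14.2.1.1 says "The following local reactions will be solicited immediately after the injection (60 minutes) and over the 7 days following the vaccination". The five items are pain, swelling, induration, erythema and pruritus, all at the injection site. Section 14.2.1.2 says "The following systemic reactions will be systematically solicited immediately after the injection (60 minutes) and during the 6 days following the vaccination". The four items are fever, drowsiness, loss of appetite and, last, "Irritability/fussiness". Section 13.4.1 gives the same two lists.

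**What is graded.** The table in section 13.4.2.2, headed "Intensity scales for solicited symptoms in infants/toddlers and children less than 6 years of age", covers these nine items and no others.

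**The fallback.** Under section 14.2.2, anything reported beyond the solicited items is an unsolicited adverse event, graded mild, moderate or severe. Item 3 of section 14.1 is narrower. It counts unsolicited events only if they arise outside scheduled visits and lead to a physician consultation.

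**The concern.** The protocol emphasises allergy in its primary criterion and names the relevant signs, but the lists that put the criterion into practice leave them out. Solicited lists decide what staff ask about and look for at every contact. A sign that nobody asked about cannot be recovered at analysis.

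This does not look like an adaptation to age. Section 13.4.1 also names headache, malaise and fatigue, which a child of 1 to 2 years cannot report, so dropping those is understandable. Urticaria, diffuse erythema and oedema are visible to an observer. The summary of the earlier adult trial in Burkina Faso reports by name that diffuse erythema, urticaria and Quincke's oedema did not occur. As written, this protocol does not provide for an equally systematic statement in children.

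**Working it through.** **1. The protocol's own figure on systemic reactions.** Section 16.2 gives the chance of seeing at least one affected child among 14 in an MSP3 arm. The formula is 1 − (1 − p)^14.

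- p = 0.15: 1 − 0.85^14 = 1 − 0.1028 = 0.897 (stated 90%)
- p = 0.11: 1 − 0.89^14 = 1 − 0.1956 = 0.804 (stated 80%)
- p = 0.19: 1 − 0.81^14 = 1 − 0.0523 = 0.948 (stated 95%)

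The statement reproduces and is not in dispute. Its p is the risk of any systemic reaction or serious event. It is not an allergic risk, so it cannot size this point.

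**2. Named signs against the lists.** There are 5 local + 4 systemic = 9 solicited items.

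| Sign named in 13.4.1 | Local list | Systemic list | Intensity table |
|---|---|---|---|
| Urticaria | no | no | no |
| Oedema | only as injection-site swelling | no | only as injection-site swelling |
| Contra-lateral reaction | no | no | no |
| Diffuse erythema | only as injection-site erythema | no | only as injection-site erythema |

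Away from the injection site, 0 of the 4 signs are covered.

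**3. Example records followed through the definitions.**

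| Event | Solicited? | Unsolicited under 14.2.2? | Item 3 of 14.1? |
|---|---|---|---|
| Non-serious generalised urticaria 20 minutes after a dose, at the vaccination visit | no | yes | no: it arises at a scheduled visit |
| Non-serious facial oedema on day 2 | no | yes | only if it arises outside a scheduled visit and needs a physician |
| Swelling at the injection site on day 2 | yes, local | no | not applicable |
| Axillary temperature 37.6 °C on day 1 | yes, systemic, grade 1 | no | not applicable |

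The first record is the kind of event that item 1 of section 14.1 emphasises. No solicited list or solicited scale implements that emphasis, and item 3 does not pick the event up. It counts as unsolicited only under section 14.2.2 and the wider wording of section 2 and the synopsis.

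**4. Elicitation after the first hour.** The section on clinical evaluation and follow-up gives the purpose of the five daily home visits as assessing solicited local and systemic reactions. The day 6 assessment is at the clinic. Nothing in the protocol text directs field workers to look for the four signs on days 1 to 5.

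**The case against.** The strongest reply is that these events are not lost, and this largely stands:

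- The 60-minute observation covers acute events of any kind (section 3 and the section on clinical evaluation), and the flow chart gives it its own row, separate from solicited recording.
- Section 13.4.2 requires every event observed or reported to be documented with time, duration, intensity and relationship. An early urticaria can therefore be placed in the first hour.
- Unsolicited events are graded under section 14.2.2, and section 2 and the synopsis make them part of the primary assessment.
- The DSMB reports tabulate unsolicited events after doses 1 and 2, alongside the solicited ones, and list all serious events. Anaphylactic shock is a ground for suspension, and acute allergic reaction is an absolute contraindication to further doses. Neither rule depends on solicited status.
- A clinician sees the child on day 6, and a full examination precedes each injection.
- The case report form, the sponsor's adverse reaction form and the SOPs are not at hand and may prompt for these signs.

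A reader might infer that the trial would report zero allergic reactions by construction, or that the solicited endpoint cannot detect allergy at all. The documents do not support either reading. No section says that immediate reactogenicity is tabulated from the nine items alone, and injection-site swelling, erythema and pruritus are solicited. Nor can the 15% of section 16.2 be turned into an expected number of allergic children. No allergic-event risk is stated, and the summary of the adult trial in Burkina Faso reports none of the generalised signs.

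The reply does not answer three things. The protocol names signs for particular attention and then leaves them out of systematic elicitation at home. It leaves them out of the solicited tables. And the wording of item 3 does not cover a non-serious reaction seen at the vaccination visit.

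**Conclusion.** The point holds as a contradiction between the stated emphasis and its implementation. Its size is a count: none of the four allergic signs in section 13.4.1, away from the injection site, is among the nine solicited items or in the intensity table. The effect is weaker and less uniform ascertainment over the days after each dose, and placement of allergic events outside the solicited summaries. It is not loss of these events from the safety data or from the DSMB's view. The size of any under-recording cannot be stated, because the documents give neither an allergic-event risk nor a detection rate.

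The conclusion rests on the protocol text. If the unseen forms already prompt for these signs, the practical gap narrows to the endpoint definition and the tables, and the sections would still need to agree. It is a moderate matter: the analysis is descriptive and the fallback routes are real, but information not asked for at the visit cannot be restored later.

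**What to change.** - Add urticaria, oedema away from the injection site, diffuse erythema and contra-lateral reaction to the solicited systemic lists in sections 13.4.1 and 14.2.1.2.
- Add the same four rows to the intensity table in section 13.4.2.2, using the mild/moderate/severe scale of section 14.2.2.
- Tabulate them by arm and dose, separately for the 60-minute and 7-day windows.
- Reconcile sections 13.4.1, 13.4.2.2, 14.1 and 14.2.1 to 14.2.2. In particular, bring item 3 of section 14.1 into line with the definition in section 14.2.2, so that an event seen at a vaccination visit has a defined place.

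The cost is four extra rows on the clinic and home-visit forms. No visit, test or member of staff is added, because each child is already observed for an hour, visited at home on five days and seen at the clinic on day 6.
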